
### Safety

According to Dutch law, the investigator reports SAEs within 15 days following notification through a government-based internet portal (Centrale Commissie Mensgebonden Onderzoek (Central Committee on Research Involving Human Subjects): https://www.toetsingonline.nl/) to the accredited institutional review board (IRB) that approved the protocol. SAEs that result in death or are life-threatening will be reported within 7 days.

Because this is an exploratory dose escalation study, an independent data and safety monitoring board (DSMB) will make recommendations on continuation of the study based on safety results, focusing on toxicity and anastomotic leakage. The DSMB consists of an expert surgeon, a radiation oncologist and a statistician and is provided, annually or after every SAE, with the raw data on the primary and secondary outcomes (including toxicity, surgical complications and survival). After the first 10 patients with LAR have undergone boost treatment, inclusion of patients scheduled for LAR will be stopped for 8 months to let the DSMB compare anastomotic leakages between boost and control arms. The 8-month period will consist of the time between sCRT to primary surgery (10–12 weeks) followed by the time between primary surgery and bowel reconstruction, including a postoperative monitoring period (16–20 weeks). Only inclusion of patients undergoing LAR will be halted during this stop, because patients undergoing APR have no risk of anastomotic leakage, owing to their permanent stoma. The DSMB analyzes the data independently of the investigators and reports their advice on continuation of the study to the sponsor, which will decide on continuation or stopping of the study.

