### Standard treatment

sCRT consists of 50 Gy (25 × 2 Gy on weekdays) combined with capecitabine. The radiation dose is delivered by intensity-modulated radiation therapy (IMRT), which is standard care in our hospital, to the planned target volume (PTV), which comprises the gross tumor volume (GTV) and clinical target volume (CTV). Target volumes are delineated on computed tomography (CT) scans, matched to- and combined with T2- and diffusion-weighted magnetic resonance imaging (DWI) according to published guidelines [20]. The CTV follows the mesorectal fascia up to the rectosigmoid curvature and stretches maximally to 4 cm caudal from the tumor, sparing the sphincter in case of a low anterior resection (LAR), or includes the sphincter complex +1-cm margin in case of an abdominoperineal resection (APR). The lymph node regions (internal iliac and obturator) stretch from the caudal end of the v. iliaca communis downward to the crossing of the internal iliac vessels under the m. piriformis, laterally limited by the pelvic muscles. The obturator region stretches from the m. obturatorius to the m. levator, ventrally limited by the ureter or dorsal side of the neurovascular bundle without inclusion of the vesiculae, uterus and vagina. Lateral and dorsal border are marked by the pelvic muscles and ventral iliac region. In addition, the presacral region stretches from the upper level of the iliac vessels to mesorectum, ventrally limited 2 cm from the sacrum, including the a. rectalis superior and excluding the neuroforamina. The PTV_CTV50_ is a non-uniform margin around the CTV according to local protocol consisting of an expansion of 13 mm ventrally, 9 mm dorsally, 10 mm laterally and 10 mm craniocaudally (Figure 2). The prescribed dose to the PTV_CTV50_ is that 95% of the prescribed dose should cover ≥99% of the PTV. Radiation is delivered with an external beam linear accelerator. For position verification, the sCRT protocol consists of cone-beam CT prior to the first three fractions and weekly thereafter.

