**Figure 2 Fig2:**
[figure not shown]
**Cumulative dose plan of boost plus standard chemoradiation fractions (left) with associated dose volume histogram (right).** Delineations of gross tumor volume (GTV) plus planned target volume (PTV_GTV_) (red), clinical target volume (CTV) plus PTV (PTV_CTV_) (green), bladder (brown) and sigmoid (pink). Areas that receive a total dose of >65 Gy are represented in orange), and those that receive >50 Gy are shown in turquoise.

Capecitabine is administered orally twice daily on treatment days at a dose of 825 mg/m^2^, taken 2 hours before each radiation fraction and 12 hours later. Hematologic toxicity is tested every 2 weeks. Surgery is performed 10 to 12 weeks postradiation according to the Dutch guidelines [19]. The decision whether to perform total mesorectal excision surgery in form of LAR or APR, is made on the basis of the location and extensiveness of the tumor [21].

Two routine MRI scans are acquired using an MRI protocol developed in house, consisting of T2-weighted and DWI image sequences [22]. The first scan (taken maximally 2 weeks prior to radiation) is used for radiation planning, and the second (obtained 9 weeks postradiation) is used for preoperative response evaluation and surgical planning. Immediately prior to surgery, the surgeon will also perform a digital rectal examination (DRE) for clinical response evaluation.

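### The 8-month pause in LAR inclusion is triggered by the boost, but its stated components start only after chemoradiation, so five weeks of sCRT go uncounted

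*Protocol article*

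**What the plan says.** The Safety section of the protocol article gives a trigger and a length: once the first ten LAR patients have undergone boost treatment, "inclusion of patients scheduled for LAR will be stopped for 8 months". The stated purpose is to let the DSMB compare anastomotic leakage between the arms. Inclusion of patients scheduled for abdominoperineal resection continues.

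The next sentence breaks the length into two parts. The first is "The 8-month period will consist of the time between sCRT to primary surgery (10–12 weeks"); the second is "followed by the time between primary surgery and bowel reconstruction, including a postoperative monitoring period (16–20 weeks").

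Three other statements fix where these parts sit on the time axis:

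- Boost intervention: the boost takes five weekdays in the week before sCRT begins, and boost plus sCRT together take 30 fractions, or 6 weeks.
- Standard treatment: "sCRT consists of 50 Gy (25 × 2 Gy on weekdays) combined with capecitabine".
- Standard treatment, on timing of the operation: "Surgery is performed 10 to 12 weeks postradiation according to the Dutch guidelines".

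Under Secondary endpoints, leakage in LAR patients is followed by daily review of postoperative charts for 30 days, and surgical complications are also recorded after closure of the diverting stoma.

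**The concern.** The clock and its contents have different origins. The clock starts when the tenth LAR patient has had the boost. The first component starts when sCRT ends, because surgery is timed from the end of radiation. The whole sCRT course lies between these two points and is not counted.

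The pause is there so that leakage in a small boosted group can be judged before more LAR patients are boosted. The protocol itself extends the period of interest through bowel reconstruction. If the fixed length runs out first, the comparison may be made with late follow-up incomplete. With ten boosted patients, each one whose follow-up is incomplete is 1/10 = 10% of the boosted group.

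**Working it through.** **Inputs.** sCRT to surgery: 10–12 weeks (Safety; Standard treatment). Surgery to reconstruction, monitoring included: 16–20 weeks (Safety). sCRT: 25 weekday fractions / 5 per week = 5 weeks (Standard treatment). Leakage chart review: 30 days = 30/7 = 4.3 weeks (Secondary endpoints). The article does not say how it converts months to weeks, so both usual conventions are shown:

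- calendar months: 365.25/12/7 = 4.348 weeks each, so 8 months = 34.8 weeks;
- four-week months: 8 × 4 = 32 weeks.

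**Step 1: the plan's own figure.** The sum of the stated components is 10 + 16 = 26 to 12 + 20 = 32 weeks. In four-week months this is 6.5 to 8.0, so the upper end reproduces 8 months exactly. In calendar months it is 6.0 to 7.4, so 8 months exceeds the components by 34.8 − 32 = 2.8 to 34.8 − 26 = 8.8 weeks.

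**Step 2: time needed from each possible starting event.** Margin = length of the pause minus time needed; a negative margin means that the pause ends first.

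| Clock starts at | Weeks needed | Margin, calendar (34.8) | Margin, four-week (32) |
|---|---|---|---|
| End of sCRT | 26–32 | +8.8 to +2.8 | +6 to 0 |
| End of boost (literal trigger) | 5 + 26 = 31 to 5 + 32 = 37 | +3.8 to −2.2 | +1 to −5 |

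**Step 3: when the shortfall appears.** From the end of the boost, it needs the two intervals together to exceed 34.8 − 5 = 29.8 weeks (calendar) or 32 − 5 = 27 weeks (four-week), out of a stated range of 26–32.

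**Step 4: leakage after primary surgery.** From the end of the boost, the 30-day window closes at 5 + 10 + 4.3 = 19.3 to 5 + 12 + 4.3 = 21.3 weeks. Both are well inside 32 or 34.8 weeks. Only the stretch around and after bowel reconstruction can fall outside the pause.

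**The case against.** The best case for the text is that the two Safety sentences should be read together. The second says what the 8 months contain and begins with the interval after sCRT, so the clock may have been meant to start at the end of chemoradiation. On that reading nothing is short. This is a fair reading, but it is not what the trigger says. The Sample size considerations section also speaks of boost treatment and sCRT as two things added together, which favours taking the trigger as the boost alone.

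Several stronger conclusions are tempting, and the objection to each of them stands:

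- *That 8 months is a plain arithmetic error.* The upper bounds total 32 weeks, which is 8 four-week months. In calendar months the pause is longer than its stated parts, which is the safe direction.
- *That leakage would be unknown when inclusion reopens.* The 30-day window after primary surgery has closed by then on every reading.
- *That no time is left for DSMB review.* From the end of the boost, this is true only toward the slow end of the ranges; at the fast end 3.8 weeks (calendar) or 1 week (four-week) remain.
- *That a further 30 days after reconstruction must be added.* The text says that the 16–20 weeks already include monitoring.
- *That LAR inclusion restarts without DSMB advice.* The article says that the DSMB advises and the sponsor decides. It does not say that inclusion resumes regardless, and restart details may be in the full protocol.

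Few patients would be affected. With 60 offers, about 80% acceptance and 3 years of recruitment, there would be 60 × 0.8 = 48 boosts in 156 weeks, or one per 3.25 weeks if evenly spread, and LAR boosts would be further apart. A 2.2-week gap would then typically touch only the tenth patient; a 5-week gap might also reach the ninth.

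The point is not one of journal condensation. The article prints the trigger, the length and the components, and they do not fit together.

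**Conclusion.** The point holds in limited form. The pause has a fixed length whose trigger and components start at different events, with 5 weeks of sCRT between them. On the literal trigger, the pause can end up to 2.2 weeks (calendar months) or 5 weeks (four-week months) before the slowest patient completes the protocol's own follow-up through bowel reconstruction. The month convention does not settle it: the one that makes the components reach 8 months is also the one that gives the larger shortfall.

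This rests on two assumptions: that having undergone boost treatment means the end of the boost week, and that the two intervals fall toward the upper part of their ranges (above 29.8 or 27 weeks combined). If the clock starts at the end of sCRT, there is no shortfall. A reader might infer that the safety comparison would be made without leakage data; the documents do not support that. What is at risk is late follow-up, probably in one or two of ten patients.

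**What to change.** Reconcile the Safety section with Standard treatment and Boost intervention. Name the event from which the 8 months run. List components that add up from that event, with the sCRT course among them if the boost is the trigger. Give 8 months as an estimate, and state that the DSMB comparison is made once the tenth boosted LAR patient has completed the follow-up that the protocol already describes.

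This takes about one sentence in the Safety section and changes no treatment. The cost is that the pause may last a few weeks longer when patients are slow to reach surgery or reconstruction.

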### Sample size considerations

On the basis of our center’s experience, we assume that 13% of patients will reach pCR if undergoing sCRT. On the basis of a prediction model published by Appelt *et al.* [30], we expect the pCR rate to be 30% after 65 Gy treatment. Because we consider this study to constitute preliminary work for subsequent studies aimed at evaluating even higher dose increases, we deem it important to find an effect if there really is one, but less important to unjustly find an effect. Therefore, we will use a one-sided α of 15% because it is unlikely that the pCR rate after boost treatment plus sCRT will be lower than after sCRT alone, in combination with a power of 80% because we do not want to increase uncertainty when a negative result is achieved. We further expect that approximately 80% of the patients who receive a boost offer will accept it. Patients who are offered the boost treatment but refuse to undergo the boost will remain in the intervention arm for analysis but receive sCRT (Figure 1). We expect no cross-over from the control arm to the intervention arm, because only patients who are randomly selected to receive a boost offer are informed about and offered it, whereas all non-selected patients undergo standard treatment (that is, sCRT) without receiving information about the boost trial. Taking into account the estimated response rates, together with a 20% refusal rate in the intervention arm, we require 60 patients per arm to demonstrate a statistically significant difference. We expect to complete recruitment within 3 years.

### Data analysis

Data will be analyzed according to the intention-to-treat principle. Data of eligible patients who were randomly offered the boost (intervention arm) will be compared with eligible patients who were not randomly selected (control arm). In case of dropout (that is, no surgery following chemoradiation), a worst-case analysis will be performed in which all non-resected intervention-arm patients are classified as non-complete responders and all non-resected control patients are classified as complete responders. However, because omission of surgery is not common practice in our institution, we expect these numbers to be small. In case of substantial boost treatment refusal in the intervention arm, complier average causal effect analysis will be performed to deal with differences in compliance with treatment between both arms [31]. Outcomes include tumor pCR rate (TRG 1), good pathological response (TRG 1–2), clinical response, grade 3–4 toxicity, QoL, recurrence rates and disease-free and overall survival.

The primary outcome (proportion of patients with pCR) will be presented in proportions and compared by means of the χ^2^ test. Toxicity will be presented as the overall and/or time point-specific incidence of grade 3–4 toxicity, and differences will be tested with the χ^2^ test. QoL will be compared at multiple points in time. A relevant change in the patient’s perspective is indicated by a 10% difference or more than 0.5 of the standard deviation [32]. QoL data will be analyzed by mixed-effects models. Differences in disease-free and overall survival rates will be analyzed by Kaplan-Meier analysis and log-rank test. Differences with a *P*-value <0.05 are considered statistically significant, except for the primary endpoint, where *P* < 0.15 has been prespecified.

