## Discussion

The RECTAL BOOST study aims to quantify the effect of an external beam radiation (EBR) boost of 15 Gy prior to standard chemoradiation (50 Gy) on pCR rates in patients with locally advanced rectal cancer. Toxicity, clinical (complete) response, (surgical) complications, (disease-free) survival, QoL and feasibility of boost delivery are secondary endpoints. In this study, we will assess in a randomized fashion whether a preoperative 65 Gy EBR-only regimen (15 Gy boost followed by 50 Gy chemoradiation) can safely increase the proportion of patients with pCR (TRG 1) in comparison with the proportion observed after 50 Gy chemoradiation alone. Although contact X-ray [34], brachytherapy, EBR and EBR-brachytherapy combined studies [6] have shown response, sphincter-saving and organ preservation benefits at doses up to 60 Gy, such benefits have not been shown for the 65 Gy dose level when reached by an EBR-only approach.

High rates of good responders are important, as this will increase the number of patients eligible for organ-preserving treatment strategies. These strategies aim to improve the QoL of patients with a good response while their good oncologic outcome, and possible survival benefits, are maintained. Nevertheless, the value of tumor regression has not yet been confirmed as a surrogate endpoint for oncologic outcome in this setting. In the present study, however, all patients, including those with a good clinical response to preoperative treatment, will still undergo surgery because pathological response is the primary endpoint, and because resection remains the standard care according to Dutch guidelines [19]. Therefore, future randomized studies in patients with good clinical responses after (boost) chemoradiation are needed to further assess the effect of radical surgery versus organ preservation on QoL, toxicity and (disease-free) survival. In this study, we aim to quantify response rate by its current gold standard (that is, pathology), which in turn can be correlated to the clinical response data that are also obtained. In so doing, this study will provide important insight into the results of dose escalation that would otherwise be lacking in a trial that would combine dose escalation and omission of surgery within the same trial.

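### At the planned 20% boost refusal, the only toxicity comparison certain to be run shows about 0.8 of any excess in boosted patients, because the complier analysis is conditional

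*Protocol article*

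**What the plan says.** Protocol article, Sample size considerations: "We further expect that approximately 80% of the patients who receive a boost offer will accept it". The same section states how the rest are handled: "Patients who are offered the boost treatment but refuse to undergo the boost will remain in the intervention arm for analysis but receive sCRT". Refusal is part of the sample size: "together with a 20% refusal rate in the intervention arm, we require 60 patients per arm". Non-compliance is expected on one side only: "We expect no cross-over from the control arm to the intervention arm".

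Protocol article, Data analysis: all data follow the intention-to-treat principle, comparing patients offered the boost with patients not selected. Grade 3–4 toxicity is compared between arms by a χ² test at P < 0.05. On compliance the section says: "In case of substantial boost treatment refusal in the intervention arm, complier average causal effect analysis will be performed". The next sentence lists the outcomes, with grade 3–4 toxicity among them. No threshold for *substantial* is stated.

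Protocol article, Discussion: the trial is to assess whether the 65 Gy regimen "can safely increase the proportion of patients with pCR (TRG 1" compared with 50 Gy chemoradiation alone.

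**The concern.** The safety question in the Discussion concerns patients who receive the boost. The comparison that is certain to be made concerns patients who are offered it. At the planned acceptance these groups differ by about 12 of 60 patients.

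For pCR, dilution works against the experimental treatment, and the sample size already allows for it. For toxicity caused by the boost, the same dilution makes the treatment look safer than it is for those who take it. The complier analysis would remove this, but it depends on an undefined word. A refusal rate that was foreseen and built into the sample size could easily be judged not substantial. The scenario the trial was designed for may therefore be the one in which the correction is not made. The article describes the trial as preliminary work for studies of still higher doses, so an attenuated toxicity estimate could carry forward into them.

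**Working it through.** **Inputs from the article (Sample size considerations).** Acceptance 80%, no control cross-over, 60 per arm, one-sided α 0.15, power 80%. For pCR: "we assume that 13% of patients will reach pCR if undergoing sCRT" and "we expect the pCR rate to be 30% after 65 Gy treatment".

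**Step 1: reproduce the 60 per arm.** Diluted intervention rate = 0.8 × 30% + 0.2 × 13% = 26.6%. The pooled-variance formula for two proportions (no continuity correction), with z = 1.036 and 0.842 and mean rate 0.198, gives:

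n = [1.036 × √(2 × 0.198 × 0.802) + 0.842 × √(0.13 × 0.87 + 0.266 × 0.734)]² / 0.136² ≈ 59.8, so 60 per arm, with power 80.1%.

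The stated figure is reproduced. The 20% refusal is a design parameter: 0.2 × 60 = 12 patients expected without the boost and 48 with it.

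**Step 2: the dilution factor.** If controls never receive the boost and the offer alone has no effect on outcome, then

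ITT difference = acceptance × difference in boosted patients,

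and the complier average causal effect (CACE) = ITT difference / acceptance.

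- pCR: 0.8 × (30 − 13) = 0.8 × 17.0 = 13.6 points.
- Attenuation is 20% at 80% acceptance, 10% at 90%, 30% at 70% and 40% at 60%.

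**Step 3: apply it to toxicity.** The article gives no grade 3–4 rates, so those below are assumptions. With 10% in controls and 25% when boosted, the intervention arm shows 0.8 × 25% + 0.2 × 10% = 22%. The ITT excess is 12 points, and 12 / 0.8 = 15 recovers the excess in boosted patients.

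**Step 4: is the low power due to dilution?** Normal-approximation power at 60 per arm, level 0.05, two-sided (sidedness is not stated and is assumed here), control rate 10%:

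| True excess if boosted | Excess shown by ITT | Power, 80% acceptance | Power, full acceptance |
|---|---|---|---|
| 10 points | 8 | 24% | 33% |
| 15 points | 12 | 43% | 58% |
| 20 points | 16 | 63% | 79% |

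With a 15-point excess and control rates of 5%, 10%, 15% and 20%, power is 56%, 43%, 36% and 32% at 80% acceptance, against 71%, 58%, 50% and 45% at full acceptance. Dilution costs some power, but most of the shortfall comes from having 60 patients per arm.

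**Step 5: precision.** For 10% against 22%, the 95% half-width of the ITT difference is 1.96 × √(0.10 × 0.90/60 + 0.22 × 0.78/60) = 12.9 points. Dividing by 0.8, with acceptance treated as fixed, gives about 16.1 points for CACE. Estimate and standard error scale together, so the CACE test has nearly the same power as ITT.

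**The case against.** A reader might infer four stronger claims. The article does not support them.

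- *Toxicity is analysed by ITT only.* The CACE sentence is not restricted to pCR, and grade 3–4 toxicity appears in the outcome list directly after it. ITT is the only *unconditional* toxicity comparison.
- *The complier analysis is triggered by results.* The trigger is refusal of the offer, which for each patient precedes the boost, chemoradiation and surgery. The method is named in advance; only the cut-off is open.
- *Harm will be understated.* This requires both that the boost raises toxicity and that the observed refusal is judged not substantial. The 20% is a planning expectation. ITT remains a valid estimate of the effect of offering the boost, which suits a pragmatic design.
- *A non-significant toxicity result is likely because of dilution.* It would be likely with no refusal at all if toxicity doubled from 10% to 20% (power 33%).

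The different significance levels (0.15 for pCR, 0.05 for toxicity) are a separate matter. The article gives a reason for the relaxed level, and neither level affects the size of the estimate.

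The strongest objection is that safety does not rest on the final χ² test. Under Safety, the data and safety monitoring board receives raw toxicity, complication and survival data annually or after every serious adverse event. The pause for a leakage comparison is triggered by patients who have actually undergone the boost. This stands for conduct during the trial. It does not define the toxicity estimate reported at the end.

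It can also be said that a numeric cut-off belongs in the analysis plan, which is not shown. That is fair for the number. But the article itself makes the correction conditional, and no cut-off is needed if the condition is dropped.

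**Conclusion.** The point holds as a cheap improvement. At the planned refusal rate, the only toxicity contrast certain to be reported estimates about 0.8 of the excess among boosted patients, which is anti-conservative for the stated safety question. The example of 15 points shown as 12 rests on assumed toxicity rates. The factor 0.8 rests on 80% acceptance, no control cross-over and no effect of the offer itself; it does not depend on the toxicity rates.

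The 3-point attenuation is small beside a half-width of about 13 points, so it will not by itself decide the safety conclusion. It is, however, a bias in a known direction that data already collected can remove. The pCR dilution is not a defect: it is built into the sample size.

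**What to change.** Delete the condition on substantial refusal. State that CACE (instrument: random selection; complier: received the boost) is always reported next to ITT for grade 3–4 toxicity, anastomotic leakage and pCR. Tabulate toxicity and surgical complications by treatment received, with boosted patients, refusers and controls in separate columns. Give risk differences with 95% confidence intervals. Keep ITT primary for pCR.

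The cost is a few extra tables from data already collected. CACE intervals are wider than those from ITT. The tables by treatment received are not randomised comparisons, so they should accompany CACE and not replace it. None of this restores power.

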## Methods/design

### Study design

This study is being conducted within the ProspectIve data CollectioN Initiative on Colorectal cancer (PICNIC) project [16]. The prospective observational PICNIC cohort includes patients with colorectal cancer of all stages. Information collected includes baseline demographic and clinical data, as well as prospective clinical follow-up and patient-reported outcome measures (PROMs). The study follows the cohort multiple randomized controlled trial (cmRCT) design [17] and provides a pragmatic infrastructure for multiple randomized controlled trials (RCTs).

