### Random selection

Patients within the PICNIC cohort who meet the above inclusion criteria form a subcohort of eligible patients (Figure 1). From among this subcohort, a random sample is selected on a 1:1 basis with varying block sizes (*n* = 6 to 8) using a centrally available computer program. Randomly selected patients are offered the experimental intervention (boost prior to sCRT) by their treating physician. If they accept the offer, they will sign an additional informed consent to receive the boost. Patients who refuse the boost will receive care as usual (that is, sCRT). Patients in the subcohort who will not be randomly selected will not be informed about the boost intervention, nor will they be informed about their participation in the control arm of this study. When the trial is completed, aggregate disclosure about the trial results will be provided to the entire PICNIC cohort at the same time.

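### The primary pCR comparison is a valid, adequately powered crude χ² test, but it makes no use of baseline stage; a prespecified covariate-adjusted analysis would bring a modest gain.

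*Protocol article*

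**What the plan says.** All references are to the protocol article.

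- **Data analysis.** "The primary outcome (proportion of patients with pCR) will be presented in proportions and compared by means of the" χ² test. No covariate is named for this comparison.
- **Random selection.** From the eligible subcohort, "a random sample is selected on a 1:1 basis with varying block sizes" of 6 to 8. No stratification factor is named.
- **Sample size considerations.** "we assume that 13% of patients will reach pCR if undergoing sCRT" and "we expect the pCR rate to be 30% after 65 Gy treatment". The error rates are "we will use a one-sided α of 15"% "in combination with a power of 80"%. The result, "together with a 20% refusal rate in the intervention arm", is 60 per arm.
- **Patient recruitment.** Stage (T3 with threatened mesorectal fascia, T4, or N2) defines eligibility, so it is known for everyone before selection.
- **Study design.** For the cohort, "Information collected includes baseline demographic and clinical data, as well as prospective clinical follow-up".
- **Standard treatment.** A routine MRI is taken at most two weeks before radiation for planning, and the gross tumour volume is part of the target volumes delineated. The article does not say that the volume is stored as a trial variable, or when delineation happens relative to random selection.

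**The concern.** With 60 patients per arm, about 24 expected complete responses and no named stratification factor, the arms can differ by chance in tumour burden. If tumour burden predicts complete response, the crude difference in the one trial that is run will carry that imbalance. The χ² test holds its error rate averaged over all possible randomisations, but it cannot correct for the one that occurs. Adjusting for a predictor fixed before selection does so, and usually recovers a little power. If covariates are chosen only after an imbalance has been seen, the choice is driven by the data, so they have to be named in advance. At stake is some precision and some robustness of the primary result, in a trial whose sponsor says that missing a true effect is the error to avoid.

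**Working it through.** **1. Reproduce the plan's own figure.** Inputs from Sample size considerations: control 13%, boost 30%, 20% refusal, one-sided α 0.15, power 0.80.

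- Intention-to-treat rate in the boost-offer arm: 0.8 × 0.30 + 0.2 × 0.13 = 0.266. Difference: 0.266 − 0.13 = 0.136. Mean rate: 0.198.
- n per arm = [z₀.₈₅ √(2 p̄ q̄) + z₀.₈₀ √(p₀q₀ + p₁q₁)]² / d² = [1.036 × √0.3176 + 0.842 × √0.3083]² / 0.136² = 1.105 / 0.0185 ≈ 59.8, so **60**.
- Power at 60 per arm: 80.1% by the normal approximation, 80.7% by exact binomial enumeration of the uncorrected one-sided test.

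The crude test therefore delivers what the plan claims for it.

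**2. Expected events.** 60 × 0.13 + 60 × 0.266 = 7.8 + 16.0 ≈ 24. This limits the number of covariates.

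**3. Size of chance imbalance.** Allocation is treated as simple randomisation.

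- Binary covariate with an assumed 50% prevalence: SD of the between-arm difference = √(0.25 × 2/60) = 9.1 points. A gap above about 1.96 × 9.1 ≈ 18 points has a 5% chance.
- Standardised continuous covariate: SD = √(2/60) ≈ 0.18.

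**4. What an imbalance does to the crude test.** Simulation of 100,000 trials per setting, 60 per arm, 80% acceptance. The odds ratios are assumptions, because the article gives none. Each cell shows an imbalance of about 1 SD / 2 SD.

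| Assumed OR per SD | Shift in crude risk difference (points) | Null rejection, imbalance favours boost | Power, imbalance against boost |
|---|---|---|---|
| 1.5 | 1.1 / 2.2 | 18% / 21% | 77% / 73% |
| 2.0 | 1.8 / 3.6 | 20% / 26% | 74% / 66% |
| 2.5 | 2.3 / 4.5 | 22% / 32% | 72% / 60% |

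The planned difference is 13.6 points. A typical imbalance moves it by 1 to 2 points; several points need both a large imbalance and a fairly strong predictor.

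**5. Power gained by adjustment, one covariate.** Logistic model with arm and one standard normal score, one-sided signed likelihood-ratio test at 0.15, 4,000 runs per setting (Monte Carlo SE of power about 0.6 point).

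| Assumed OR per SD | Power, crude | Power, adjusted | Null rejection, crude | Null rejection, adjusted |
|---|---|---|---|---|
| 1.0 | 80.0% | 80.2% | 14.2% | 14.6% |
| 1.5 | 79.9% | 80.2% | 14.1% | 14.6% |
| 2.0 | 80.6% | 82.1% | 14.9% | 15.0% |
| 2.5 | 80.4% | 82.9% | 15.0% | 15.3% |

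**6. The two-covariate model.** With 3,000 runs per setting and assumed odds ratios of 1.0 to 2.5, the gain was about 0 to 3 points, and under 1 point for stage alone. Null rejection was about 16–17% adjusted against 15–16% crude. A further set (5,000 runs, 40% cT4 assumed) with weaker effects gave 80.8% to 80.9% with no effect, 81.1% to 81.3% at odds ratios of 1.3 per SD and 1.5 for cT4, and 81.1% to 82.0% at 1.65 and 2.0.

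**The case against.** The strongest case against is that nothing here is wrong. The χ² test is valid under randomisation, it matches the sample size calculation, and its error rate already allows for chance imbalance on average. The trial calls itself exploratory. The article condenses a fuller protocol, and stratification details or a supportive adjusted analysis may sit there or in an analysis plan. All of this stands, and it limits the point to the one thing the article does fix: a crude primary test.

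A reader might infer more, and the documents do not support it:

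- **That the trial falls short of its power because it does not adjust.** It does not: 80.1% is reached without covariates.
- **That tumour volume is recorded for everyone and is ready to use.** The article describes delineation for planning and does not say that the volume is a trial variable. Boost intervention describes delineation on T2-weighted and diffusion-weighted MRI, while Standard treatment describes CT matched to and combined with MRI. If the volume is drawn after random selection by staff who know the arm, it may depend on the arm, and adjusting for it could introduce bias.
- **That stage or volume is a strong predictor of pCR.** The article gives no figure, and eligibility already narrows the range of stage.

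The objection does not remove protection against the imbalance that actually occurs. That benefit remains when the average power gain is small, in proportion to how strongly the covariate predicts response.

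A separate matter in the same section weighs more: the threshold of 0.15 is given there without a side. Read as two-sided, power at 60 per arm falls to 66.9%, far more than adjustment could recover.

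**Conclusion.** The point holds as a minor improvement to a stated method. The primary analysis is unadjusted and no stratification factor is named, while stage is available for every patient before selection. Prespecified adjustment is worth about 0 to 3 points of power, under 1 point if stage is the only covariate, and guards against a shift in the crude difference of typically 1 to 2 points. When the covariates are weak, no material power is lost. These sizes rest on assumed odds ratios of 1.0 to 2.5, assumed prevalences, 80% acceptance and simple randomisation. The planned χ² result would remain interpretable if nothing were changed.

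**What to change.** Before outcomes are compared by arm, prespecify as primary analysis a logistic model for pCR with arm and at most two baseline covariates whose values are fixed before random selection:

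1. cT4 against other stage.
2. Tumour volume, only if it is measured on the pre-treatment planning MRI in the same way in both arms and without knowledge of the arm. Otherwise leave it out.

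Report the standardised (marginal) risk difference with a confidence interval, so that the effect stays on the scale used for the sample size, and test it one-sided at 0.15. Keep the crude χ² comparison as a sensitivity analysis. If the sponsor prefers to keep χ² as primary, prespecifying the adjusted model as supportive would still give most of the protection.

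The cost is wording in the analysis plan, plus reading the volume under those conditions if it is used. The downsides are a model-based primary analysis on about 24 expected events, which is why two covariates is the ceiling, and a null rejection rate up to about 1 point higher in simulation. Sample size, eligibility and treatment are untouched.
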